### 2.1. Patients

The trial includes adults with a diagnosis of low-risk CVD with class I heart failure according to the NYHA (New York Heart Association) functional assessment criteria (24), diagnosed by the Cardiology and Rehabilitation team of the Hospital of Melilla. Patients must live in Melilla during the intervention phase, have mobile technology with an internet connection at home (including one of the following devices: desktop personal computer, laptop, tablet, or smartphone), and be able to access email or instant messaging frequently and reliably. Patients who suffered non-mild cardiac events prior to the first contact with this research, those whose pathologies are not classified as CVD, and those subjects who are not in full cognitive capacity that allows them to use new technology tools will be excluded. Patients will be excluded if they have any absolute or relative contraindications to exercise testing as per the American Heart Association guidelines [20]. Inclusion and exclusion criteria is show in Table 1.

In order to generate sufficient data for the development of this research, a sample size of (*n* = 30) patients will be recruited. The primary aims of this sample size determination is to evaluate whether the proposed intervention is feasible, safe, and effective. A larger randomized controlled trial that would have adequate power could be designed based on what was learned in this study. The strategies to achieve an adequate inclusion of participants that reach the target sample size include the multidisciplinary collaboration of the team from the Regional Hospital of Melilla (Cardiology Department, Head of the Rehabilitation Service and the Physiotherapy team). The collaborators were informed about the characteristics of the study in personal interviews and presentation. We ensured that the recruitment of patients has a socio-demographic diversity in relation to their social origin, gender, ethnicity, and education adapted to the particularities of the reference population. For the development of this research, an intentional non-probabilistic type of sampling will be used for the convenience of the study, due to the characteristics of the subjects. This trial has the approval of the Andalucía Ethics Committee with HIP version 17112020.

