
#### 2.3.2. Secondary Explanatory Variable

Satisfaction and usefulness: The acceptance and usefulness of telemedicine applications is a prerequisite for identifying the potential clinical benefits of this technology. It is therefore important to complement this research with tools that examine patient satisfaction and perception [29]. An adaptation of the Telemedicine Satisfaction and Usefulness Questionnaire (TSUQ), whose psychometric analysis supports construct validity and internal consistency reliability, and which is available in English and Spanish, will be used [29]. The instrument used showed high reliability (Cronbach’s alpha 0.8) and evidence of validity with respect to perception in telemedicine [30]. It includes 17 questions that are assessed with a 5-point Likert subjective scale (1 totally disagree and 5 completely agree). The individual obtains scores from 17 to 85. The higher the score, the better the perception of the telerehabilitation intervention. Therefore each of the scores of the 17 variables indicated and finally the total score of the Test will be analyzed [29,30].

Analysis of the cost-effectiveness: To assess the cost-effectiveness of the telerehabilitation intervention, the international guidelines for conducting cost analyses in randomized clinical trials will be followed [31]. Such an economic analysis is based on the health sector perspective, which means that only costs corresponding to health interventions will be considered, and not related costs to the patient. Therefore, only costs related to the provision of health services will be taken into account [32].

Costs are divided into two categories of variables: firstly, costs related to clinical aspects (direct costs) and secondly, costs related to the use of the technology (indirect costs).

Direct costs: Numerical variable calculated on the basis of the number of hours of intervention and the cost of the physiotherapist according to the hourly wage in the health system in the centers where the research is carried out. It will be calculated based on the recording of the number of sessions in both groups.

Indirect costs: Numerical variable calculated based on the cost of using the technology for the telerehabilitation platform.

Adherence and safety: Participants will be advised to report and record barriers of use and any adverse event during the study. Number of sessions are automatically registered by the CTR tool.

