### 2.4. Data Collection Procedure, Monitoring, and Management

Once participants have been informed and agree to participate in the study, data will be collected for statistical analysis. This data collection will take place in the period February–June 2021. Initial assessment (Pre) and final 8-week assessment (Post) will be carried out by the research team with the cardiology, rehabilitation, and physiotherapy departments. The data will be aggregated to a research database created for this purpose and managed by the principal’s research using exportable data tables for statistical analysis. 

The research is designed in 4 stages, as presented in Figure 1 in a study design flow diagram:

Stage 1 includes 2 different processes: firstly the identification of candidates, the provision of prior information and the signing of informed consent in the event that the subjects agree to participate. Secondly, the assessments by the cardiology department with ergometry and biochemistry test at (T0-Pre). This stage ends with the referral to the rehabilitation department.

Stage 2 includes: the assessments by the rehabilitation department with quality of life, functional capacity outcomes, and comorbidity index added to previous clinical information. At this stage, the Modified Borg Scale Education is offered to participants to assess their level of fatigue during exercise. A personalized CTR program is proposed according to the Physiotherapy Department. This stage ends with the referral to the Physiotherapy department and CTR staff.

Stage 3 includes: 8 weeks CTR program with the supervision of the Physiotherapy Department and the CTR staff. An initial 1-to-1 session is offered with technology management and patient education. Daily follow up sessions include the progression, barriers of use, and adverse event records. CTR team will updates programs according to participant’s feedback and rehabilitation supervision.

Stage 4 includes: Final assessments and evaluation (T1-Post). At this stage, cardiology, rehabilitation, physiotherapy and principal research are compiled into the results of clinical and self-reported outcomes after 8 weeks CTR program including: biochemistry, ergometry, quality of life, and functional capacity. At this stage, satisfaction and usefulness, economic data safety, and adherence records will be added to research data’s for statistical analysis

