### 2.5. Statistical Analysis

This research is a single center prospective controlled trial pre/post design. The results of the trial research will be presented as a summary of the outcome measures, together with the estimated effect size and precision. Statistical analysis will be performed according to the intention-to-treat principle. Patient characteristics will be summarized using frequencies and percentages for categorical factors, and using means and standard deviations for continuous measures in order to have as much information as possible available for exploration and analysis. The effect sizes will be calculated using Cohen’s d, so that the results can be compared to other studies. The outcome measures will be compared before and after the completion of the 8-week CTR program. All statistical analyses will be conducted using SPSS software. Statistical significance was set at *p* < 0.05.

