## 3. Results

Enrollment began in February 2021. First study results will be reported in the middle of 2021. Recruitment is currently underway. The recruitment goal is 30 cardiac rehabilitation patients. Data collection is anticipated to be complete by July 2021.

If the results confirm beneficial effects in biochemical, cardiac function, quality of live, and functional capacity, the effectiveness of the intervention will be proven in patients with heart failure. The successful delivery of the intervention, the absence of significant adverse effects, and the user satisfaction will demonstrate the feasibility of these interventions in cardiac patients.

The results of this study will determine if a larger-scale intervention is feasible. Further, this pilot study will be the first to examine the effect of CTR intervention on patients in a cardiac rehabilitation setting in Melilla (Spain). The results of this study will provide differences compared to previous research: first of all, its implementation in the autonomous city of Melilla (located on the African continent with particular demographic characteristics); secondly the use of the innovative CTR platform based on the App Physiotec; thirdly, the collection of outcomes that combine clinical, self-reported and economic data and lastly, automated treatment adherence registry.

This study will add more evidence in support of the use of CTR program as an effective tool in new cardiac rehabilitation programs.

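### No adverse effects in 30 patients cannot demonstrate absence of harm: the exact 95% upper limit for 0/30 is still 11.6%, so Section 3 should carry a bound

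*Protocol article*

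**What the plan says.** Section 2.1 sets the sample at 30 patients and says of this number: "The primary aims of this sample size determination is to evaluate whether the proposed intervention is feasible, safe, and effective". No calculation accompanies it. The next sentence leaves adequate power to a larger randomised trial that could be designed from what is learned here.

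Section 3 repeats the target ("The recruitment goal is 30 cardiac rehabilitation patients") and says how the findings will be interpreted. After successful delivery of the intervention it lists two further conditions: "the absence of significant adverse effects, and the user satisfaction will demonstrate the feasibility of these interventions in cardiac patients". No tolerable event rate or confidence limit is tied to this statement, and the word *significant* is not defined.

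On how events are collected, Section 2.3.2 says: "Participants will be advised to report and record barriers of use and any adverse event during the study". Sections 2.2 and 2.4 add daily recording of incidents, an initial one-to-one session and supervision by physiotherapy and telerehabilitation staff. Table 2 lists adherence and safety as a secondary outcome. Section 4 counts failure to improve, poor adherence and exercise at too high a workload among the possible adverse events.

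**The concern.** A study of 30 patients followed for 8 weeks gives little information about uncommon events. If the reading of the result is fixed beforehand so that an empty adverse event record helps to demonstrate something, the conclusion treats no observed events as evidence of no meaningful risk. How much risk remains open depends on the sample size, and the article does not say how much that is.

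What is at stake is what the trial may conclude. No estimate or test of the primary outcomes is affected. A feasibility verdict that requires absence of harm inherits the uncertainty about harm, and the interpretation in Section 3 leaves that uncertainty out.

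**Working it through.** **Inputs**
- Sample size: 30 (Sections 2.1 and 3).
- Events: 0, the scenario that Section 3 describes as "the absence of significant adverse effects".
- Follow-up: from the initial assessment to the one at 8 weeks (Section 2.4).
- Confidence level: 95%. Section 2.5 says "Statistical significance was set at *p* < 0.05" without giving sidedness, so both versions are shown.
- True event rates: none in the article. The 1%, 2%, 5% and 10% below are assumptions for illustration.

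**The plan's own figure.** The 30 cannot be reproduced. No event rate, tolerable rate, effect size or power is given for it.

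**Upper limit with no events.** The exact (Clopper-Pearson) limit solves (1 − p)^n = α/2 (two-sided) or α (one-sided):
- Two-sided: 1 − 0.025^(1/30) = 0.1157, or 11.6%.
- One-sided: 1 − 0.05^(1/30) = 0.0950, or 9.5%.
- Cross-checks: the Wilson two-sided limit is 11.4% and the rule of three gives 3/30 = 10.0%.

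The article gives no dropout rate, so 30 is the best case. If only 27 or 24 patients were followed (assumed numbers), the two-sided limit would be 1 − 0.025^(1/27) = 12.8% or 1 − 0.025^(1/24) = 14.2%.

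**Chance of a clean record at a given true rate**, (1 − p)^30:

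| Assumed true rate | P(0 of 30) |
|---|---|
| 1% | 0.99^30 = 0.740 |
| 2% | 0.98^30 = 0.545 |
| 5% | 0.95^30 = 0.215 |
| 10% | 0.90^30 = 0.042 |

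**Patients needed for zero events to exclude a given rate**, n = ln(α/2)/ln(1 − p), rounded up (ln(α) for one-sided):
- 5%: ln(0.025)/ln(0.95) gives 72; one-sided 59.
- 2%: ln(0.025)/ln(0.98) gives 183; one-sided 149.

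So 30 patients without an event make a rate well above 10% implausible, but remain compatible with a rate of several percent.

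**The case against.** The strongest reply is that Section 3 speaks of feasibility, not safety. Absence of adverse effects is one of three conditions that must hold together, and the verb attached to safety in Section 2.1 is *evaluate*. That stands. A reader might infer that the plan will declare the programme proven safe on a zero count; no sentence says so. The statement in Section 3 that something will be proven concerns effectiveness.

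The second reply is that the limitation is acknowledged. Section 2.1 leaves adequate power to a later trial, Sections 3 and 5 call the study a pilot, and Section 4 names larger trials as future work. This also stands and makes the point milder. It does not remove it, because Section 3 keeps the stronger verb despite that acknowledgement.

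The third reply is that Section 2.5 promises precision for the outcome measures, safety is a listed outcome, and the choice of interval may sit in a full plan that is not shown. The point therefore does not rest on a missing interval. It rests on a published interpretation that 30 patients cannot support whichever interval is computed.

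Three further inferences go beyond the article:
- *That zero events are likely.* No event rate is given, and under the broad list in Section 4 a zero count is not obviously to be expected.
- *That the safety record would be used to justify wider use.* The abstract and Section 4 mention guidelines and policy, but tie neither to a safety finding.
- *That events rest only on self-report during unsupervised exercise.* Patients do train on their own from videos, but Sections 2.2 and 2.4 describe daily recording and staff supervision.

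**Conclusion.** The concern holds in a limited form. Safety is a stated purpose of the 30-patient sample, and an empty record of significant adverse effects is one of three joint conditions said to demonstrate feasibility, with no bound attached. With 0 of 30 the data remain compatible with a true rate of up to 11.6% (two-sided 95% limit; 9.5% one-sided), and a clean record would be seen in about 55% of such studies at a true rate of 2% and about 21% at 5%. A zero count therefore cannot demonstrate absence of harm.

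The limits assume that all 30 patients are followed, that each is counted once, and that events in different patients are independent with a common probability. The 2% and 5% rates are illustrative, but the conclusion does not depend on either of them.

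The change is worth making because it alters what the trial may conclude, although it leaves the design and the primary analyses as they are.

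**What to change.** **Section 2.1:** word the safety aim as a preliminary estimate of the adverse event rate.

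**Section 3:** for the adverse event component, replace the claim of demonstration with text such as: *The number and proportion of patients with at least one significant adverse event will be reported with an exact 95% confidence interval. If none occurs in 30 patients, the data are compatible with a rate of up to about 12% (two-sided limit), and the conclusion on safety is left to the larger trial.* If fewer than 30 are followed, the limit should be recalculated for the number actually observed.

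**Definition:** say which events count as significant, and count harms separately from the failure to improve and poor adherence that Section 4 lists alongside them. Otherwise the proportion has no clear numerator.

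**Cost:** wording in two sections, one definition and one interval, on data already being collected. The real price is a less favourable stated conclusion.

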## 4. Discussion

Telemedicine has the promise of improving quality, increasing patient access, and reducing health care costs [34], and recent advances in telecommunications technologies have boosted the possibility of carrying out rehabilitation processes over the internet [35]. Studies have shown that telerehabilitation is effective in improving clinical outcomes in various pathologies, suggesting that increasing the intensity provided by telerehabilitation is a promising option to be offered to patients (32). This research should provide knowledge about the possibility of implementing CTR programs in the hospital environment, identifying the health resources and costs allocated to define new intervention policies in this group of patients. Unlike other studies that require software implementations in specific devices, our intervention generates few obstacles since it is available in any device that allows internet connection and that patients usually have (PC, laptop, tablet, smartphone), allowing access from any location and different devices prioritizing the use of mobile health. This contrasts with other studies that require a highly complex technological platform, software installation, and multidirectional cameras for controlled clinical control connecting the healthcare provider and the patient [36].

Technical problems (disconnection, device failures) and technological difficulties may arise in connection with the use of technology. However, staff members are available to provide technical support by phone or email, without the need to visit the patient at home to install or check any hardware. As possible adverse events, we considered the lack of improvement and positive evolution of the patient as well as the appearance of a low level of adherence. We also considered as an adverse event the performance of exercise with excessive workload. Patients will be informed of the importance of warning the health professional of any incident or setback in their recovery and their right to withdraw from participation in the research at any time.

Future lines of research would involve the development of clinical trials with a large sample size; a qualitative approach to attend focus groups to explore their thoughts and concerns about the intervention. Themes will be constructed from the data to give insight into the experiences of the different participant groups. As participation is important for rehabilitation departments, it is essential to include the participants’ perspective in the evaluation of the treatment. Finally, the opportunity to develop a multicenter randomized clinical trial with comparison groups performing in-hospital or home-based rehabilitation programs has the aim of identifying the most appropriate intervention.

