Patients are initially supervised by the research team who will conduct 1-to-1 training sessions to ensure proper execution of the exercises and encourage patient adherence. Patients are instructed to perform self-training by following the video exercises through the CTR program. At the beginning of the study, advice is given on general care, in physical activity and issues concerning drug intake.

Patients are advised to refrain from any other specific training during the intervention period. Any deviations from the adherence and practice of the CTR program are recorded daily, noting any adverse incidents.

The TR group receives a personalized program for 8 weeks, including at least one session per day and is done through a web and mobile application. The telerehabilitation application allows health professionals to create personalized exercise programs, hold video conferences with patients, generate videos, images and parameters of each exercise, as well as send them by email and follow up patients through the mobile application.

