## Figures and Tables

**Figure 1 ijerph-18-04038-f001:**
[figure not shown]
Study design. Abbreviations CVD, cardiovascular disease; CTR, cardio-telerehabilitation.

**Table 1 ijerph-18-04038-t001:** Inclusion and exclusion criteria.

Inclusions Criteria	Exclusions Criteria
Adult over 18 Years old	Cognitive ability not suitable for the use of technologic tools.
Diagnosis: Ischemic heart disease in New York Heart Association (NYHA) functional class I-II with preserved global systolic function or in intermediate range (LVEF > 40%) after revascularized acute coronary syndrome.	
Lives in Melilla during the research period.	Absolute or relative contraindications to exercise testing
To have mobile technology with an internet connection at home (including one of the following devices: desktop personal computer, laptop, tablet, or smartphone)	
Ability and knowledge to access email or instant messaging	

Abbreviations LVEF, Left ventricular ejection Fraction.

**Table 2 ijerph-18-04038-t002:** Primary and secondary outcomes.

	Definition	Type
Primary Outcomes		
Biochemical	Hematies Level, Glucose, Creatine Kinase (CK), Triglycerides, Total Cholesterol, High Density Lipoprotein Cholesterol (HDL-C), Low Density Lipoprotein Cholesterol (LDL-C), Glycated Hemoglobin (HbA1c)	Clinical
Cardiac Function	Metabolic Equivalent (MET), Resting Heart Rate (RHR), Maximum Heart Rate (HRmax), Final Heart Rate (FHR), Rating Scale for Perceived Exertion (RPE), Systolic Blood Pressure (SBP), Diastolic Blood Pressure (DBP)	Clinical
Quality of Life	SF-12, EQ-5D	Self-Reported
Functional Capacity	Duke Activity Status Index (DASI)	Self-Reported
Secondary Outcomes		
Feasibility, Satisfaction and Usefulness	Telemedicine Satisfaction and usefulness Questionaire (TSUQ)	Self-Reported
Cost-Effectiveness	Direct Costs/Indirect Costs	€/Self-Reported
Adherence and Safety	Nº of sessions completed and adverse events record	Automatized App record

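### The adverse-event list includes lack of improvement, low adherence and excessive workload, so the safety record mixes efficacy and adherence with harm

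*Protocol article*

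**What the plan says.** Section 4 (Discussion) of the protocol article is the only place that says what kinds of event count. Its list reads: "we considered the lack of improvement and positive evolution of the patient as well as the appearance of a low level of adherence". The next sentence adds: "We also considered as an adverse event the performance of exercise with excessive workload". No threshold is given for any of the three.

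Elsewhere the reporting is open-ended. Section 2.3.2 says: "Participants will be advised to report and record barriers of use and any adverse event during the study". Section 2.2 says: "Any deviations from the adherence and practice of the CTR program are recorded daily, noting any adverse incidents". The Discussion also tells patients of the importance of "warning the health professional of any incident or setback in their recovery". In Section 2.4, the daily follow-up of Stage 3 includes adverse-event records, and Stage 4 adds the safety records to the data for analysis.

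Table 2 puts adherence and safety in one row, covering completed sessions and the adverse-event record, with the source given as "Automatized App record". Section 2.3.2 says only of the session count that the tool registers it automatically.

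Section 3 (Results) lists successful delivery first among its grounds for feasibility and goes on: "the absence of significant adverse effects, and the user satisfaction will demonstrate the feasibility of these interventions in cardiac patients".

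**The concern.** A safety outcome should count harm. Here the listed items are a failure to benefit, a failure to take part and an excess of exposure. A patient who stops exercising and does not improve could be recorded under efficacy, under adherence and as an adverse event, although nothing medically untoward has happened.

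Safety is one of the stated purposes of the 30-patient sample (Section 2.1), identifying adverse events is a secondary aim, and the result feeds the feasibility conclusion in Section 3. If the record follows the Discussion's list, a high count may show only that the programme was poorly followed or had little effect. A low count may reflect good adherence as much as good tolerance. Neither can be read as safety without unpicking the entries afterwards.

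**Working it through.** The article states no adverse-event rate and no figure derived from one, so there is nothing to reproduce. The check sets the listed items against the outcomes and then sizes the overlap.

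**Items against outcomes**

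| Item in the Discussion | Where it already belongs | A medical harm in itself? |
|---|---|---|
| Lack of improvement | Pre/post comparison of the primary outcomes (Sections 2.3.1 and 2.5) | No |
| Low adherence | Adherence part of the Table 2 row (sessions completed) | No |
| Excessive workload | Deviation from the prescribed exercise, no threshold | No, though relevant to safety |

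**Are medical harms excluded?** No. The wording in Sections 2.2, 2.3.2 and 4 covers any adverse event, incident or setback, and a medical event falls within each.

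**Are they kept apart from the three items?** No section says so. Section 2.2 records adherence deviations and adverse incidents in one sentence, and Table 2 has a single adverse-event record.

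**Size of the mixing (illustration)**

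- Input from the article: n = 30 (Sections 2.1 and 3).
- Assumption: a share *a* of patients with low adherence, taken as 10% to 30%, each giving one entry. Entries from low adherence = n × a, so 30 × 0.10 = 3 and 30 × 0.30 = 9.
- Assumption: a true medical event rate *s* of 2% to 10%, one entry per affected patient. Entries = n × s, so 30 × 0.02 = 0.6 and 30 × 0.10 = 3.
- Medical share of these two kinds of entry: lowest 0.6 / (0.6 + 9) = 6%, highest 3 / (3 + 3) = 50%.

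Thus, across these ranges, medical harms make up at most half of the entries before any patient is added for lack of improvement or excessive workload.

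**What a clean record could show**

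For 0 events in 30 patients, the exact two-sided 95% upper limit is 1 − 0.025^(1/30) = 0.1157, or 11.6%. This concerns the sample size and would be the same under a perfect definition. It matters only for how Section 3 words its conclusion.

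**The case against.** The strongest reply is that the Discussion's sentence speaks of possible adverse events and is not an exclusive definition, while the operative methods text is open-ended. That stands as far as capture goes. A reader might infer that medical harms are not recorded, or that the safety data are unusable, but the article supports neither: harms can be reported and could be interpreted if tabulated separately. The reply does not answer the mixing. The Discussion assigns the three items to adverse events, and no other section takes them out.

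A reader might also see a conflict between patient self-report (Section 2.3.2) and an app record (Table 2), or infer that harm is missed once a patient stops logging in. Section 2.2 has incidents and feedback entered in the telerehabilitation tool, so the two can be one route, and Section 2.4 provides daily follow-up with adverse-event records as well as the T1 assessment. What remains is a loose label: Table 2 calls the whole row automatic, when only session counts are described that way.

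It is tempting, too, to say that a zero count would be nearly impossible because some patients always fail to improve. That needs a rule that any non-positive change on one outcome is an adverse event, which the article does not state.

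Finally, the article specifies a record and not a pooled count, and Section 3 uses the narrower idea of significant adverse effects. This is fair, but the article never says how the significant ones are to be picked out of the record. The lack of seriousness and relatedness grading is detail that an article may leave to the full protocol, and it is not held against the plan here.

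**Conclusion.** The point holds in a limited form. The article states a classification that puts an efficacy result, an adherence outcome already listed in Table 2 and an exposure deviation among the adverse events. Harm is not excluded from the record, but it is not distinguished within it, so the feasibility argument in Section 3 rests on a mixed quantity. On an assumed 10% to 30% low adherence, that item alone contributes 3 to 9 entries among 30 patients with no medical harm. The classification problem itself does not depend on those rates.

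The 11.6% limit is not evidence of a faulty definition. It shows only that a clean record in 30 patients would not by itself carry the word demonstrate, which fits the article's own statement that adequate power is left to a larger trial.

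This should be fixed, but it is not critical: safety is a secondary outcome of a pilot, open-ended reporting is in place, and the remedy is mostly wording.

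**What to change.** 1. In Section 4, and wherever adverse events are defined, restrict the term to untoward medical occurrences.
2. Report lack of improvement with the efficacy outcomes, low adherence with the adherence outcome, and excessive workload as a separate deviation.
3. In Table 2, keep the automatic app source for session counts only. Give the source of adverse events as patient report together with the daily and T1 contacts, and say that this covers patients who stop using the app.
4. In Section 3, replace the claim that absence of events will demonstrate feasibility with the number of patients with medical adverse events out of 30 and its exact 95% confidence interval.

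The cost is revised wording and one small table. The contacts already exist, and no change to the sample or the visit schedule is needed. Events already recorded can be sorted into these categories when tabulated.
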